### **3.5 Treatment**

Any adverse events happen, appropriate care or medical treatment (if necessary) should be immediately provided to keep the safety of all participants. In addition, all adverse events and serious adverse events and treatment should be recorded and reported to the Principal Investigator and the Committee within 24 hours and complete the case report form.

## **4. Data management**

### **4.1. Case report form**

All case report forms for each participant should be filled out by study staff in a timely manner. The case report form should be double-checked for potential errors or missing data prior to patients leaving the clinic. All data, including screening assessments, questionnaires, physical examinations, and laboratory examinations, will be filed in the participant’s chart. Original documents, participants’ charts, and CRF forms will be stored in the study office.

### **4.2. Data entry**

All data will be double-entered by researcher staff. Two sets of databases will be generated and tested for consistency using the SAS program. Whenever inconsistencies are found, the data will be corrected by re-examination of the original case report forms or laboratory reports.

### **4.3 Data reports**

Several standardized reports will be generated as follows: 1) participant recruitment and follow-up; 2)

demographics; 3) data quality and monitoring; 4) adverse events. These reports will be used for study management. These reports will be blinded to research personnel who collect study outcomes.

## **5. Statistics**

### **5.1 Estimation of sample size**

The study will enroll 800 participants, who will be randomly allocated to the mobile messaging-based intervention or control group in a 1:1 ratio. The primary outcome comprised the mean changes in HbA1c levels, LDL-C levels, and SBP levels from baseline to 12 months simultaneously modeled for a single overall treatment effect(26). We anticipate 80% statistical power to detect a 5% difference of the net change in standardized overall treatment effect at a significance level of 0.05 using a 2-tailed test; this corresponds to detect a detectable difference of 0.5% in HbA1c change ( $7.2\pm1.6\%$ ), 5 mm Hg in systolic blood pressure ( $132\pm18$  mmHg at baseline) and 0.25 mmol/L in LDL-C ( $2.94\pm0.96$  mmol/L)(27-29). Assuming a dropout rate of 20% over 12 months, we will recruit 400 subjects to each group in the proposed clinical trial.

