## 60 2.3 Study Population.

### 61 2.3.1 Inclusion criteria

62 Patients will be eligible if they are adults over 18 years old with poorly control Type 2 diabetes mellitus  
63 (defined as  $HbA1c \geq 7\%$  or if combined with clinical  $CVD \geq 7.5\%$ ) comorbid with at least one risk factor for  
64 CVD (such as  $SBP \geq 140$  mmHg and / or diastolic blood pressure (DBP)  $\geq 90$  mmHg  $\geq$  and / or  $LDL-C \geq$

100mg/dL) or clinically diagnosed ASCVD (such as acute coronary syndrome, ischemic stroke, Transient ischemic attack or peripheral artery disease). All participants had access to a smartphone to read and accept text messages. All participants would provide written informed consent at the initial trial visit.

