#### **5.2.1 Data analysis plan**

Data was analyzed according to participants' randomization assignments, regardless of their subsequent status (intention to-treat principle). All the analyses will be conducted using SAS version 9.4 (SAS Institute Inc). Group differences in the trial outcomes will be evaluated using the general linear model for continuous variables and the chi-square test for categorical variables. Continuous variables will be presented as mean  $\pm$  standard deviation (SD) or median (interquartile range), and categorical variables will be presented as frequencies with percentages. In this study, the overall intervention effect on HbA1c, LDL-C, and SBP will be tested using a scaled marginal model, in which each outcome was scaled by its SD. Generalized estimating equations will be used to calculate the regression coefficient and outcome-specific scale variables in SAS PROC GENMOD, and the assumption of an overall intervention effect will be tested using a score test(30). Group differences for the secondary outcomes will be also evaluated with the use of the generalized estimating equations for continuous variables adjusting for baseline levels corresponding to each study outcome. In addition, the correlations of outcomes among participants within each clinic center using an exchangeable

correlation structure will be also taken into account in the analysis. Multiple imputations for missing data in the multivariable analyses will be conducted using the Markov chain Monte Carlo method.

Subgroup analyses of HbA1c, LDL-C, and SBP will be also conducted according to age ( $\leq 60$  and  $> 60$  years), sex (male and female), education levels (junior high school degree or below, high school education or above), employment status (never worked/unemployed, retired and on duty), smoking status (never, former and current), current drinking (yes or no), prevalent obesity (yes or no), prevalent hypertension (yes or no), prevalent hypercholesterolemia (yes or no). A two-sided P value less than 0.05 is considered statistically significant.

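### The 80% power in section 5.1 cannot belong to the 5% standardized effect, which is about 5.7 times smaller than the component differences said to correspond to it

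*Protocol*

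**What the plan says.** Section 5.1 (Estimation of sample size) anticipates "80% statistical power to detect a 5% difference of the net change in standardized overall treatment effect". The test is two-sided at 0.05. It then ties that effect to three component differences: "this corresponds to detect a detectable difference of 0.5% in HbA1c change" (listed with 7.2 ± 1.6%), 5 mmHg in SBP (132 ± 18 mmHg, labelled as baseline) and 0.25 mmol/L in LDL-C (2.94 ± 0.96 mmol/L). On numbers it says: "Assuming a dropout rate of 20% over 12 months, we will recruit 400 subjects to each group".

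Section 5.2.1 (Data analysis plan) fixes the scale of the overall effect. The three outcomes are "tested using a scaled marginal model, in which each outcome was scaled by its SD", so the overall effect is in SD units. Section 5.1 gives no separate SD of change and no correlation between the three outcomes.

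Section 2.3.1 (Inclusion criteria) admits patients "with poorly control Type 2 diabetes mellitus", defined as HbA1c of at least 7%, or at least 7.5% with clinical CVD.

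**The concern.** Section 5.1 presents one target effect in two forms, with one power figure for both. On the SD scale that the analysis uses, 5% is most naturally 0.05 SD. The listed differences, divided by the SDs beside them, come to between a quarter and a third of an SD. Both descriptions cannot be the effect for which the trial has 80% power.

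This bears on the single primary test. A null result could be read against a target of 0.05 SD (0.08% HbA1c, 0.9 mmHg, 0.048 mmol/L) or against one nearly six times larger. The protocol does not let a reader choose between them.

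**Working it through.** **Inputs.** From section 5.1: two-sided 0.05; power 80%; 400 per arm, 20% dropout, so 400 × 0.8 = 320 evaluable per arm; the differences and SDs above. From section 5.2.1: each outcome scaled by its SD. Assumed, because not stated: inter-outcome correlation ρ, varied from 0 to 1; and the SD of change, taken first as the listed SD and then as √2 times it (baseline and 12-month values uncorrelated).

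**1. Both effects on one scale.**
- HbA1c: 0.5/1.6 = 0.3125 SD
- SBP: 5/18 = 0.278 SD
- LDL-C: 0.25/0.96 = 0.260 SD
- Mean: 0.284 SD; 0.284/0.05 ≈ 5.7, and 5.7² ≈ 32, the ratio of required sample sizes.

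For the differences to equal 0.05 SD, the SDs would have to be 10% HbA1c, 100 mmHg and 5 mmol/L. With SDs √2 larger the mean is 0.284/1.414 ≈ 0.20 SD, still four times 0.05.

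**2. The other reading of 5%.** As a share of the listed means, 5% is 0.36% HbA1c, 6.6 mmHg and 0.147 mmol/L. The listed differences are 6.9%, 3.8% and 8.5% of those means, so this reading does not fit either.

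**3. Power of the overall test.** For a common effect d on three SD-scaled outcomes, SE = √[(2/n)(1+2ρ)/3], and power = Φ(d/SE − 1.96) plus the small opposite tail. At n = 320, SE is 0.0456 for ρ = 0 and 0.0791 for ρ = 1.

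| Effect | ρ = 0 | ρ = 0.3 | ρ = 0.5 | ρ = 1 |
|---|---|---|---|---|
| 0.05 SD | 19.5% | 13.9% | 12.1% | 9.7% |
| Listed differences, listed SDs as SDs of change | >99.9% | 99.8% | 99.3% | 94.8% |
| Listed differences, SDs of change √2 larger | 99.3% | 93.5% | 87.4% | 71.8% |
| Effect with 80% power (listed SDs as SDs of change) | 0.13 SD | 0.16 SD | 0.18 SD | 0.22 SD |

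With all 400 per arm analysed, 0.05 SD has 10.9% to 23.2% power; one-sided testing on top of that gives at most 34%.

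**4. Evaluable patients per arm for 80% power**, n = 2(1.96+0.84)²(1+2ρ)/(3d²): 0.05 SD needs about 2,094 (ρ = 0) to 6,280 (ρ = 1); 0.284 SD needs 66 to 196.

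**5. Can the 80% with 400 per arm be reproduced?** Not from the stated inputs for the overall test. Two unstated single-outcome calculations come close:
- HbA1c alone with SD 1.6√2: 79.8% power at 320; 322 evaluable needed, 403 with dropout.
- LDL-C alone at 0.05/3: 81.6% power at 320; 309 evaluable needed, 387 with dropout.

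Neither is the overall test at 0.05, and neither explains the 5%.

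**6. The HbA1c input.** If 7.2 ± 1.6% is a baseline distribution and roughly normal, Φ((7 − 7.2)/1.6) = Φ(−0.125) ≈ 45% of it lies below 7%. The eligible part has mean about 8.4 and SD about 1.0.

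**The case against.** The strongest reply concerns the listed differences. Section 5.1 gives no SD of change, and it labels the SBP figure as baseline. Using the listed SDs as SDs of change amounts to assuming a baseline-to-12-month correlation of 0.5, which is stated nowhere. A reader might infer from the first calculation that power for the listed differences is at least 95% and that 80% is simply wrong in the other direction. The document does not support that. Even with the listed SDs the overall test has 94.8% at ρ = 1, and components tested singly have 97.7% (HbA1c), 94.0% (SBP) and 90.9% (LDL-C). With no baseline-to-follow-up correlation the overall figure runs from 99% down to 72%. Several combinations give 80%, for example ρ = 1 with a baseline correlation of about 0.18, or ρ = 0.73 with none. This part of the reply stands.

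A reader might also infer that the correlation between outcomes was ignored. That cannot be known: the protocol only does not state it, and such detail may sit in a statistical analysis plan that is not at hand.

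On HbA1c, the ± figure stands beside the word change and is not labelled baseline; it may come from the cited studies, and follow-up values can fall below 7%. The mismatch is therefore conditional. The smaller SD in eligible patients would raise power, not lower it.

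None of this rescues the 5%. A larger SD of change leaves power for 0.05 SD the same, or lowers it if the 0.05 is in units of the listed SDs, and the two effects remain far apart.

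**Conclusion.** The point holds. That 0.05 SD is not 0.26 to 0.31 SD follows from the protocol's own figures and its own scaling, with 5% read as 0.05 SD; the percentage-of-mean reading fails too. The stated 80% cannot hold for the 5% effect: power is about 10% to 19% at 320 per arm for ρ between 1 and 0. For the listed differences, 80% is conservative under most assumptions but cannot be reproduced from the inputs given.

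A reader might go on to conclude that the trial is underpowered. The document does not show that. Very low power follows only if 0.05 SD is the true target, and the listed differences indicate a much larger one. The defect is that the target effect, its claimed equivalents and the power figure do not fit together. The HbA1c mismatch is secondary.

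**What to change.** Keep 800 patients and rewrite the one paragraph in section 5.1:

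- Delete the 5% figure and the statement that the component differences correspond to it.
- State the target overall effect in SD units. For the listed differences with the listed SDs this is about 0.28 SD.
- Give the SD of 12-month change in patients who meet the entry criteria, and the assumed inter-outcome correlation.
- Restate the power that follows from those inputs. The 80%-power effects in the table above are a guide only, and should not be copied into the protocol before the SDs are settled.
- Say whether 7.2 ± 1.6% is a baseline distribution; if it is, check that planning SD against the HbA1c entry criterion.

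The cost is one recalculation and one paragraph, with no change to enrolment, the test or the significance level.

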#### **5.2.1 Data analysis plan**

Data was analyzed according to participants' randomization assignments, regardless of their subsequent status (intention to-treat principle). All the analyses will be conducted using SAS version 9.4 (SAS Institute Inc). Group differences in the trial outcomes will be evaluated using the general linear model for continuous variables and the chi-square test for categorical variables. Continuous variables will be presented as mean  $\pm$  standard deviation (SD) or median (interquartile range), and categorical variables will be presented as frequencies with percentages. In this study, the overall intervention effect on HbA1c, LDL-C, and SBP will be tested using a scaled marginal model, in which each outcome was scaled by its SD. Generalized estimating equations will be used to calculate the regression coefficient and outcome-specific scale variables in SAS PROC GENMOD, and the assumption of an overall intervention effect will be tested using a score test(30). Group differences for the secondary outcomes will be also evaluated with the use of the generalized estimating equations for continuous variables adjusting for baseline levels corresponding to each study outcome. In addition, the correlations of outcomes among participants within each clinic center using an exchangeable

correlation structure will be also taken into account in the analysis. Multiple imputations for missing data in the multivariable analyses will be conducted using the Markov chain Monte Carlo method.

Subgroup analyses of HbA1c, LDL-C, and SBP will be also conducted according to age ( $\leq 60$  and  $> 60$  years), sex (male and female), education levels (junior high school degree or below, high school education or above), employment status (never worked/unemployed, retired and on duty), smoking status (never, former and current), current drinking (yes or no), prevalent obesity (yes or no), prevalent hypertension (yes or no), prevalent hypercholesterolemia (yes or no). A two-sided P value less than 0.05 is considered statistically significant.

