## **2. Research Design and Methods**

### **2.1 Overall design**

This study is a parallel, randomized, multicenter clinical trial with 800 participants in 5 hospitals in China with 12-months follow-up. Eligible participants with uncontrolled type 2 diabetes will be randomly assigned to the mobile messaging-based intervention or usual care for 12 months. The primary outcome comprised the mean changes in HbA1c levels, LDL-C levels, and systolic blood pressure (SBP) levels from baseline to 12

51 months simultaneously modeled for a single overall treatment effect.

[figure not shown]

52 Figure 1. study design

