## 53 2.2 Randomization and masking

54 Eligible participants were randomly assigned to either the mobile messaging-based intervention or control  
55 group in a 1:1 ratio. Randomization was stratified by study centers and performed centrally at the Research and  
56 Data Coordinating Center in Nanfang Hospital. The randomization schedules were generated using the PROC  
57 PLAN procedure in SAS statistical Software with a block size of six (Version 9.4). The research nurses,  
58 investigators, and statisticians were blinded to the treatment allocation. The clinical outcomes were also  
59 collected by blinded research doctors during the study period.

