92 The primary outcome comprised the mean changes in HbA1c levels, LDL-C levels, and SBP levels from  
93 baseline to 12 months simultaneously modeled for a single overall treatment effect.

94 **2.5.2 Secondary outcomes**

- 95 ● Change in HbA1c levels
- 96 ● Change in fasting blood glucose (FBG) levels
- 97 ● Change in lipid levels, included total cholesterol (TC) levels, triglycerides (TG) levels, high-density

- lipoprotein cholesterol (HDL-C) levels
- Change in blood pressure levels
- Change in body-mass index (BMI).
- Proportion of participants with controlled HbA1c, LDL-C, and BP levels at 12 months.
- Change in self-reported medication adherence measured by the Morisky medication adherence scale (MMAS).
- Change in health-related quality of life measured according to the 12-item Short-Form Health Survey Questionnaire.

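### The 12-month control rates are assigned a chi-square test, which uses neither baseline level nor the promised within-centre correlation: valid, but it gives up some power

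*Protocol*

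**What the plan says.** Section 2.5.2 lists among the secondary outcomes the "Proportion of participants with controlled HbA1c, LDL-C, and BP levels at 12 months". The section does not state cut-offs for control, or whether three separate rates or one joint rate is meant.

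Section 5.2.1 evaluates group differences in the trial outcomes by a general linear model for continuous variables and "the chi-square test for categorical variables". It then assigns secondary outcomes to "generalized estimating equations for continuous variables adjusting for baseline levels corresponding to each study outcome". No adjusted model is named for a binary outcome.

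The next sentence of 5.2.1 adds that "the correlations of outcomes among participants within each clinic center using an exchangeable" structure will be taken into account. It is not limited to continuous outcomes. Section 2.2 states that "Randomization was stratified by study centers", and section 2.1 describes a "multicenter clinical trial with 800 participants in 5 hospitals in China".

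**The concern.** The control rates are dichotomies of variables that are measured at baseline and analysed elsewhere in the plan with baseline adjustment. Beyond the HbA1c criterion, section 2.3.1 requires only one of raised blood pressure, raised LDL-C or ASCVD, so participants will differ in where they start on SBP and LDL-C. A participant's starting level then plausibly predicts whether the goal is met at 12 months, and a test that leaves it out loses power.

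There is also a mismatch inside 5.2.1. A Pearson chi-square test has no place for a within-centre correlation structure. Either the centre sentence does not apply to the binary outcomes, or the chi-square sentence does not fully describe their analysis. As written, the control rates stand on a different footing from the continuous results for the same variables.

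**Working it through.** **No figure to reproduce.** Section 5.1 sizes the trial for the continuous primary outcome and states no power for the control rates. The usable inputs are:
- 400 per arm with 20% dropout: 400 × (1 − 0.20) = 320 evaluable per arm; two-sided alpha 0.05.
- HbA1c 7.2 (SD 1.6), difference 0.5; SBP 132 (SD 18), difference 5 mmHg; LDL-C 2.94 (SD 0.96), difference 0.25 mmol/L.
- Five centres (section 2.1).

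**Assumptions not in the protocol.** Values are normal. Goals are HbA1c below 7%, SBP below 140 mmHg and LDL-C below 100 mg/dL (about 2.59 mmol/L, entered as 2.6), the complements of the limits in sections 1 and 2.3.1. Blood pressure control is represented by SBP alone. The baseline to 12-month correlation is 0.3, 0.5 or 0.7. The between-centre SD is 0 or 0.3 outcome SDs.

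**Chi-square power by hand.** With goal c, the control-arm rate is p0 = Φ((c − mean)/SD) and the intervention-arm rate is p1 = Φ((c − mean + difference)/SD). Power ≈ Φ((p1 − p0)/√(2p̄(1 − p̄)/320) − 1.96).
- SBP: p0 = Φ(8/18) = 0.672; p1 = Φ(13/18) = 0.765; difference 0.093; standard error 0.0356; ratio 2.62; power Φ(0.66) ≈ 75%.
- LDL-C: p0 = Φ(−0.34/0.96) = 0.362; p1 = Φ(−0.09/0.96) = 0.463; difference 0.101; standard error 0.0389; ratio 2.60; power Φ(0.64) ≈ 74%.

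**Simulation.** Each cell used 2,000 trials of 320 per arm in five equal centres, balanced within centre. Each trial was analysed by the chi-square test and by logistic regression on arm, baseline value and centre. The Monte Carlo standard error of one power figure is about √(0.75 × 0.25/2000) ≈ 1 point. Ranges run over the two centre SDs; the HbA1c rows restrict baseline to 7% or more.

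| Outcome | Correlation | Chi-square | Baseline + centre |
|---|---|---|---|
| SBP | 0.3 | 70.4-74.4% | 74.0-76.7% |
| SBP | 0.5 | 71.9-72.7% | 78.9-79.7% |
| SBP | 0.7 | 71.9-74.7% | 87.4-87.9% |
| LDL-C | 0.3 | 71.8-73.0% | 76.4-76.5% |
| LDL-C | 0.5 | 71.2-74.4% | 80.0-81.5% |
| LDL-C | 0.7 | 71.1-74.0% | 87.5-88.4% |
| HbA1c | 0.3 | 88.2-89.1% | 89.6-89.8% |
| HbA1c | 0.5 | 89.7-90.8% | 92.8-92.9% |
| HbA1c | 0.7 | 94.4-96.5% | 96.7-98.2% |

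Compared at the same centre SD, the SBP and LDL-C gains are about 2-5, 6-9 and 13-16 points at correlations 0.3, 0.5 and 0.7. The HbA1c gain is about 1-3 points. Adjusting for centre alone adds 0-2 points, so nearly all of the gain comes from the baseline value.

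**With eligibility applied.** The SBP and LDL-C rows use the unselected section 5.1 distributions. Keeping only simulated participants with HbA1c of 7% or more plus raised SBP or raised LDL-C (variables independent) reduces the gains to about 1-2, 5-7 and 10-15 points. About 57% then start below 140 mmHg, against Φ(8/18) = 67% unselected, and only about 15% start at the LDL-C goal. The DBP and ASCVD entry routes were not modelled and would raise the LDL-C figure.

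**Joint control.** If the outcome means all three goals together, adjusting for all three baselines changes power by about −1 to +2 points.

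**Validity.** In null simulations (4,000 per cell) the chi-square test rejected in 4.5-5.3% of trials.

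**The case against.** The strongest reply is that nothing here is invalid. An unadjusted comparison of randomised proportions is legitimate and holds its error rate. The outcome is one of several secondary outcomes, and section 5.1 claims no power for it. That stands: the point concerns efficiency and consistency, not error.

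A reader might infer that the plan ignores centre altogether. It does not: the within-centre correlation sentence in 5.2.1 is general. What can be said is that a chi-square test cannot deliver it, and that little power depends on centre in any case.

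A reader might also infer that the control rates will come with no effect estimate. Section 5.2.1 reports categorical variables as frequencies with percentages, from which a crude risk difference and its interval follow. The choice of effect measure is commonly left to the statistical analysis plan, which is not at hand. Only an adjusted analysis is absent, because the protocol names a different one.

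Finally, the size depends on a correlation that the protocol does not give, and the larger gains appear only at 0.7. That also stands, and is why a range is shown.

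**Conclusion.** The point holds as a modest loss of efficiency on a secondary outcome, together with two sentences in 5.2.1 that do not fit each other for binary outcomes. Taking the unselected and eligibility-restricted calculations together, baseline adjustment would raise power for SBP and LDL-C control by about 1-5 points at correlation 0.3, 5-9 at 0.5 and 10-16 at 0.7. HbA1c control gains little because entry already requires 7% or more, and joint control gains almost nothing.

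The direction was the same for SBP and LDL-C at every correlation tried. The size rests on assumed correlations and cut-offs, normality, and SBP standing in for blood pressure. It should not be read as bias or an inflated error rate, nor as resting on many participants starting at the LDL-C goal: with eligibility applied as above, few do.

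**What to change.** In 5.2.1, analyse each 12-month control rate by logistic regression on arm, the baseline value of the same variable and centre as a fixed factor. For blood pressure, enter baseline SBP and DBP; for a joint-control outcome, enter all component baselines. State which reading of the outcome is meant. Report the standardised risk difference beside the odds ratio, each with a 95% CI, and keep the chi-square test for descriptive tables. With five centres, fixed centre effects are preferable to an exchangeable working correlation with a robust variance.

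The cost is a sentence or two of text and a few lines of code; the covariates are already collected. The small downside is that the conditional odds ratio needs the risk difference beside it to be read properly. Priority is low.

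### No baseline covariate is named for the primary scaled marginal model, although secondary continuous outcomes are adjusted for baseline; precision is given up at no saving

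*Protocol*

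**What the plan says.** Sections 2.1, 2.5.1 and 5.1 define the primary outcome as change: "The primary outcome comprised the mean changes in HbA1c levels, LDL-C levels, and SBP levels from baseline to 12 months", combined into one overall treatment effect.

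Section 5.2.1 then gives three statements on continuous outcomes:

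- A general one: "Group differences in the trial outcomes will be evaluated using the general linear model for continuous variables". No covariate is named. The same sentence assigns the chi-square test to categorical variables.
- The primary test: "the overall intervention effect on HbA1c, LDL-C, and SBP will be tested using a scaled marginal model". GEE is the fitting method, and the test is described thus: "the assumption of an overall intervention effect will be tested using a score test". On scaling, the text reads "in which each outcome was scaled by its SD". No covariate is named here either.
- The secondary outcomes: also evaluated by GEE, "for continuous variables adjusting for baseline levels corresponding to each study outcome".

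Two of the three primary components return as secondary outcomes in section 2.5.2: "Change in HbA1c levels" and "Change in blood pressure levels", the latter covering SBP. LDL-C change is not in the secondary list, which names TC, TG and HDL-C. Section 5.2.1 also accounts for correlation within centres through an exchangeable structure.

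**The concern.** Baseline adjustment is attached to the secondary outcomes only. The primary model is described in some detail and has none, so an analyst following the text would fit the three changes on treatment alone.

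An unadjusted change score subtracts the whole baseline difference between arms. When the regression of the 12-month value on baseline has a slope below 1, that is too much: the estimate carries avoidable noise and responds to chance imbalance. The baselines needed to remove that noise are already measured (sections 2.6.1 and 2.6.2).

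A smaller, separate matter is that the continuous secondary outcomes fall under both the general linear model sentence and the baseline-adjusted GEE sentence, and nothing says which governs. That leaves a choice open after results are seen.

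**Working it through.** **Inputs from section 5.1.** Differences and SDs: HbA1c 0.5 and 1.6; SBP 5 and 18 mmHg; LDL-C 0.25 and 0.96 mmol/L. There are 400 per group with 20% dropout, so 400 × 0.8 = 320 evaluable per arm. The test is two-sided at 0.05.

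**Assumptions (not in the protocol).** r, the baseline-to-12-month correlation, is 0.3 to 0.7. c, the correlation between outcomes, is 0.1. The stated SDs are taken as single-time-point SDs, equal at baseline and 12 months; section 5.1 labels only the SBP figure as a baseline value.

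**The plan's own figure.** The protocol gives no figure for the effect of adjustment. Its 80% power with 400 per group is not reproduced from the stated differences and SDs: 80% power needs 161 (HbA1c), 204 (SBP) or 232 (LDL-C) evaluable per arm. That is a separate issue; 320 per arm is used below.

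**Step 1: variance.** For SD s at both times:

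- Change score: 2(1 − r)s²
- Baseline-adjusted: (1 − r²)s²
- Ratio: (1 + r)/2

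| r | Ratio | Variance cut | SE cut | Adjusted n per arm matching 320 unadjusted |
|---|---|---|---|---|
| 0.3 | 0.65 | 35% | 19% | 208 |
| 0.5 | 0.75 | 25% | 13% | 240 |
| 0.7 | 0.85 | 15% | 8% | 272 |

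Check for HbA1c at r = 0.5: the SE of the unadjusted change is 1.6 × √1 × √(2/320) = 0.126, and adjusted it is 1.6 × √0.75 × √(2/320) = 0.110. A simulation of 4,000 trials gave 0.127 and 0.110. Mean estimates agreed (about −0.50 for both at a true effect of −0.5), and type I error was about 5% for both.

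**Step 2: chance imbalance.** The SE of a baseline difference is √(2/320) = 0.079 SD, so an imbalance of at least 0.1 SD in a given component has probability 2[1 − Φ(0.1/0.079)] ≈ 21%. An imbalance of 0.1 SD moves that component's change-score estimate by (1 − r) × 0.1, which is 0.05 SD at r = 0.5. The planned standardized effects are 0.5/1.6 = 0.3125, 5/18 = 0.278 and 0.25/0.96 = 0.260, so the shift is 16% to 19% of them. If only one of three equally weighted components is imbalanced, the pooled effect moves by about 0.05/3 = 0.017 SD.

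**Step 3: consequence for the primary test.** The average standardized effect is (0.3125 + 0.278 + 0.260)/3 = 0.284. The average of three scaled outcomes has SD √((1 + 2c)/3) = √0.4 = 0.632. Power without adjustment is Φ(0.284/[√(2(1 − r)) × 0.632] × √160 − 1.96). With adjustment, the first term is divided by √((1 + r)/2), keeping c at 0.1 for the residuals.

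| r | Planned effects: unadjusted | Planned effects: adjusted | Half the planned effects: unadjusted | Half the planned effects: adjusted |
|---|---|---|---|---|
| 0.3 | 99.8% | >99.9% | 67% | 84% |
| 0.5 | >99.9% | >99.9% | 81% | 91% |
| 0.7 | >99.9% | >99.9% | 96% | 98% |

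The gain is negligible at the planned effects and real at half of them.

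**Step 4: sensitivity to equal SDs.** With k = baseline SD/12-month SD, the variance ratio is (1 − r²)/[(1 − r²) + (k − r)²]. At r = 0.5 and k = 0.7, 1.0 and 1.3 it is 0.75/0.79 = 0.95, 0.75/1.00 = 0.75 and 0.75/1.39 = 0.54. It never exceeds 1, so in large samples adjustment does not cost precision. The HbA1c entry threshold (section 2.3.1) may narrow the baseline spread and so shrink the gain for that component.

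**The case against.** The strongest reply is that nowhere does the protocol say the primary analysis is unadjusted. A change outcome is compatible with a baseline covariate, the word *also* in the secondary sentence leaves the point open, and a statistical analysis plan that is not shown may list covariates. This stands in part: the absence of adjustment is inferred from the text. Still, the paragraph describes the primary model closely and reserves baseline adjustment for the other tier, so no adjustment is its natural reading.

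Three stronger readings are tempting and are not supported.

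- A reader might infer that the primary and secondary analyses systematically disagree. Under randomization both are unbiased for the same mean difference. In the HbA1c simulation their significance verdicts differed in 0.1% to 7% of trials at the 0.5 effect and in 6% to 24% at a 0.3 effect (r from 0.7 down to 0.3). That reflects precision and chance, not bias. Regression to the mean acts on both arms alike.
- A reader might infer that HbA1c and SBP receive two conflicting estimates. The primary model yields one pooled effect in SD units, which is a different parameter from a component effect.
- A reader might infer that two tests compete for the primary hypothesis. Section 5.2.1 specifically gives it one model and one score test. The overlap of general linear model and GEE concerns the secondary continuous outcomes.

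It is also fair to object that the variance formula rests on equal SDs and that power at the planned effects is already high. Both points stand and limit the size of the finding.

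**Conclusion.** The point holds as one of efficiency and clear specification, not of validity. Followed as written, the primary model forgoes a variance reduction of 15% to 35% per component, for assumed r of 0.7 down to 0.3 and equal SDs. With unequal SDs the reduction could be much smaller or larger (5% to 46% at r = 0.5 for k of 0.7 to 1.3). At the protocol's own effects the primary conclusion is barely touched. If true effects are about half those planned, power falls short of what adjustment would give by roughly 2 to 17 percentage points (c = 0.1). The lack of one governing model for secondary continuous outcomes is stated in the text itself and needs no assumption.

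**What to change.** In section 5.2.1:

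1. State that the primary scaled marginal model includes each component's own baseline value, with an outcome-specific coefficient.
2. State which SD does the scaling. Adding covariates can change it from a marginal to a residual SD, and with it the meaning of the standardized effect in section 5.1.
3. Name the baseline-adjusted GEE as the single governing model for secondary continuous outcomes, replacing the general linear model wording. Do not delete that sentence outright: it carries the chi-square test, which is the only method stated for the secondary control proportions.

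This point requires no change to the handling of centre, which the exchangeable correlation already addresses. The cost is a protocol amendment and some programming, with no new data. The changes should be fixed before unblinded outcome data are examined.
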